### Safety assessments

All subjects will be questioned about adverse events during the treatment at each visit, and all adverse events reported will be analyzed, regardless of the investigators’ assessments of causality. Safety will be assessed by complete blood cell count, erythrocyte sedimentation rate, blood chemistry, and urinalysis.

### Randomization and blinding

Random assignment will be performed after consent is obtained using a computer-generated, blocked random-allocation sequence with a 1:1 ratio. The trial will be blinded to both patients and assessor. We will designate an independent researcher who is blinded to the interventions to be the assessor.

### Sample size

Calculation of sample size is based on previous studies assessing the efficacy and safety of Weishi Bitong Xifang fumigation for mild and moderate KOA in patients [22]. Group sample sizes of 73 and 73 achieve 90% power to detect a difference of 0.7 between the null hypothesis that both group means are 30 mm (VAS score uses a 100-mm linear measure) and the alternative hypothesis that the mean for the placebo group is 23 with estimated group standard deviations of 12 and 13 and with a significance level (alpha) of 0.05 using a two-sided test. The number of patients actually provides less than 90% power, assuming a withdrawal rate of 20%. Therefore, we will recruit a total of 168 patients; 84 patients in each group.

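### The recruitment target does not carry the stated 20% withdrawal: 84 per group leaves about 67, six short of the 73 that the plan gives for 90% power

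*Protocol article*

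**What the plan says.** The Sample size section of the protocol article builds the target in three steps.

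- Base number: "Group sample sizes of 73 and 73 achieve 90% power". The planning values are means of 30 and 23 on the 100-mm VAS, "estimated group standard deviations of 12 and 13", and a two-sided 0.05 level. The test is not named.
- Withdrawal: "The number of patients actually provides less than 90% power, assuming a withdrawal rate of 20"%.
- Target, introduced as the consequence of the withdrawal sentence: "we will recruit a total of 168 patients; 84 patients in each group".

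The total of 168 also appears in the abstract and under Recruitment and consent. The section prints the difference to be detected as 0.7, although its two means differ by 7.

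**The concern.** The section presents 84 as what 73 becomes once 20% withdrawal is allowed for. A reader who applies the stated rate to the stated target does not get back to 73. The base number, the rate and the target cannot all be right as printed, and the section does not show which one was meant.

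At stake is the 90% power statement. If withdrawal runs at the planned rate and withdrawn patients drop out of the analysis, the trial ends with fewer evaluable patients than the number to which the plan attaches 90% power.

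**Working it through.** **Inputs, all from the Sample size section:** 73 per group for 90% power; means 30 and 23; standard deviations (SDs) 12 and 13; two-sided alpha 0.05; withdrawal 20%; target 84 per group. The 1:1 ratio is under Randomization and blinding. For power I take the difference as 30 − 23 = 7 mm. Taken literally, 0.7 would need about 6,712 per group, so it reads as a misprint.

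**1. The plan's 73.** Normal approximation: n per group = (SD₁² + SD₂²)(1.960 + 1.282)²/7², where the squared sum is about 10.51.

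- SD 13 in both groups: 338 × 10.51/49 ≈ 72.5, so 73. Power at 73 is 90.2%.
- SDs 12 and 13: 313 × 10.51/49 ≈ 67.1, so 68. The t-test needs 69.
- Rank test under normality, SDs 12 and 13: 69/(3/π) = 72.3, so 73. Power at 73 is 90.7%.
- t-test with SDs 12 and 13: power at 73 is 91.9%.

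So 73 follows from two ordinary routes, and on the t-test with the printed SDs it gives more than 90%.

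**2. The withdrawal step.** This uses only 73, 20% and 84, so neither the effect size nor the test matters.

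- Correct inflation, n/(1 − d): 73/0.80 = 91.25, so 92 per group, 184 in total.
- The cruder n × (1 + d): 73 × 1.20 = 87.6, so 88 per group, 176 in total.
- Remaining from the stated target: 84 × 0.80 = 67.2, about 67 per group; 73 − 67 = 6 short.
- Withdrawal that 84 does cover: 1 − 73/84 = 13.1%.

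Neither inflation rule turns 73 and 20% into 84.

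**3. Power at 67 per group, 7 mm, two-sided 0.05.**

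| Method | Power at 67 |
|---|---|
| Normal approximation, SDs 12 and 13 | 89.95% |
| t-test, SDs 12 and 13 | 89.5% |
| Rank test, SDs 12 and 13 | 88.1% |
| Normal approximation, SD 13 | 87.6% |
| t-test, SD 13 | 87.2% |

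The shortfall against 90% runs from practically nothing to about 3 percentage points.

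**The case against.** The strongest reply is that the power loss may never occur. The Statistical analysis section defines the intent-to-treat population as all randomized subjects given at least one treatment, and VAS is measured at baseline and three later visits. A patient who withdraws late need not leave that population. If all 84 per group are analysed, t-test power with SDs 12 and 13 is 95.0%. How missing values are handled may be set out in a fuller plan that is not shown. This stands as a limit on the consequence: 67 is the number left if every withdrawn patient is lost, not a certain analysed number. It does not remove the contradiction, because the Sample size section itself treats withdrawal as a loss of power and offers 84 as the remedy.

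Two stronger readings are tempting, and the documents support neither.

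- A reader who works only with SDs 12 and 13 gets 68 or 69 and might infer that 73 is wrong. The section names no test; 73 follows from SD 13 or from a rank test, and it is sufficient on the t-test.
- A reader might notice that 67/0.80 = 83.75 rounds up to 84 and infer that 73 and 84 come from different calculations. But 73 × 1.15 = 83.95 also rounds to 84, which would make the withdrawal rate the odd figure. The document does not decide between them.

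**Conclusion.** The point holds as an inconsistency between three printed figures. At the plan's own 20% rate, 84 per group leaves about 67, six below 73; 73 with 20% withdrawal would need 92 per group; 84 covers about 13%. That part is plain arithmetic and needs no assumption.

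The power figures rest on two assumptions: that the printed 0.7 means 7 mm, and that withdrawn patients are not analysed. On those, power is about 87% to 90% instead of 90%. The severity is minor. The planned design and analysis can stand; what is wrong is the statement of what 168 patients deliver.

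**What to change.** Keep 168. In the Sample size section, reconcile 73, 20% and 84, and name the test and the SD behind 73. Then do one of the following.

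- Keep the 20% rate: state that it leaves about 67 per group and give the power for the named method. For a t-test with SDs 12 and 13 that is 89.5%; other choices give about 87% to 90%.
- Keep 73: state that 84 per group allows for about 13% withdrawal.

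The choice belongs to the sponsor, who knows how 73 was obtained; 73 should not be deleted, nor a test assumed, on the strength of this check. The restated sentence should also settle whether the difference is 7 mm, since the power depends on it.

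The cost is about one sentence and no extra patients. The only downside is a slightly less favourable stated power or withdrawal allowance.

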### Statistical analysis

The data will be collected and analyzed according to the intention-to-treat principle. We will compare baseline characteristics in both groups. Efficacy analyses will be performed for both the intent-to-treat population and per-protocol population. The intent-to-treat population will consist of all randomized subjects who have been administered at least one treatment. In a per-protocol analysis, only patients who complete the entire clinical trial according to the protocol are counted in the final results. Primary outcome will be compared between both groups. The extent and time pattern of rescue medication will be reported in each randomized group; when comparing the underlying outcomes of the rescue medication, we assume the use of rescue medication varies with time, to allow for dependence within patients, so we adopt a multilevel regression approach with rescue as a time-dependent covariate [23]. Micro-perfusion alteration outcome will be compared using Student’s *t*-test. All statistical analyses will be performed using SAS 9.2 software (SAS Institute Inc, Cary, NC, USA). All statistical tests will be two-sided, and the level of significance will be set at 0.05.

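### Baseline VAS is measured on every patient, but neither the sizing nor the stated primary analysis uses it; naming a baseline-adjusted model would add precision at no cost, by an amount that depends on an unstated correlation

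*Protocol article*

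**What the plan says.** All of the following is in the protocol article.

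- **Primary outcome measure:** VAS pain on a 100 mm line, recorded at baseline and at the 1-, 2- and 4-week visits.
- **Inclusion criteria:** entry VAS of at least 20 mm, with no upper limit.
- **Randomization and blinding:** a "blocked random-allocation sequence with a 1:1 ratio". No stratification by pain is mentioned.
- **Sample size:** "Group sample sizes of 73 and 73 achieve 90% power to detect a difference of 0.7", from means of 30 mm and 23 mm with "estimated group standard deviations of 12 and 13", "with a significance level (alpha) of 0.05 using a two-sided test". Withdrawal is taken as 20%, and 84 per arm (168 in total) are to be recruited. The section gives no correlation between baseline and follow-up, and does not say whether the SDs are for final scores or for change.
- **Statistical analysis:** "Primary outcome will be compared between both groups". No test, model, covariate or visit is named for VAS. The same paragraph names Student's t-test for micro-perfusion and a multilevel regression, with rescue use as a time-dependent covariate, in connection with rescue medication. The only stated use of baseline data is a comparison of baseline characteristics between groups.

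**The concern.** Baseline pain usually predicts later pain. A comparison of follow-up VAS that ignores it leaves the explained part of the between-patient variation in the error term. It also lets part of any chance baseline difference into the treatment estimate. The planned effect is 7 mm, entry pain can lie anywhere from 20 to 100 mm, and no stratification by pain is described, so both effects matter here.

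The sample size has little margin. The Sample size section itself concedes less than 90% power once withdrawal is allowed for, and 84 per arm does not fully cover 20% withdrawal from 73. Baseline adjustment is a standard way to gain precision without enrolling anyone, and the data are already collected. The one-sentence primary analysis also leaves open the choice between final score, change score and adjusted score.

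**Working it through.** **Inputs from the Sample size section.** Difference 30 − 23 = 7 mm. SDs 12 and 13, root mean square √((12² + 13²)/2) = 12.51. Two-sided alpha 0.05, power 90%, 73 per arm, 20% withdrawal, 84 recruited per arm. **Assumed, not in the documents:** the baseline to follow-up correlation r, shown from 0.2 to 0.6.

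**1. The plan's own figure.** n per arm = 2·SD²·(1.960 + 1.282)²/7².
- SD 13 in both arms gives 72.5, rounded up to 73, which matches the plan. The t-test gives 74.
- SD 12.51 gives 67.1, rounded up to 68. The t-test gives 69.

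The stated 73 therefore fits SD 13 in both arms, and both SD readings are carried forward.

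**2. Completers.** 84 × 0.8 = 67.2, so 67 per arm, 6 short of 73. Covering 20% withdrawal would need 73/0.8 = 91.25, or 92 per arm.

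**3. Effect of adjustment.** If the SDs are for final scores, the residual SD is SD·√(1 − r²). Power is from the noncentral t distribution with 67 per arm and 7 mm:

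| r | Variance removed (r²) | Power, SDs 12 and 13 | Power, SD 13 in both |
|---|---|---|---|
| 0 (unadjusted) | 0% | 89.5% | 87.2% |
| 0.2 | 4% | 90.7% | 88.4% |
| 0.3 | 9% | 92.1% | 90.0% |
| 0.5 | 25% | 96.0% | 94.7% |
| 0.6 | 36% | 98.0% | 97.2% |

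**4. Break-even.** 67 adjusted completers match 73 unadjusted when 67/(1 − r²) = 73, so r = √(1 − 67/73) = 0.287, about 0.29. At r = 0.5, 67 completers are worth 67/0.75 = 89 unadjusted.

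**5. Chance imbalance.** No baseline SD is given. Assuming 12.5 mm, the standard error of the baseline difference at 67 per arm is 12.5·√(2/67) = 2.2 mm, so gaps of 2 to 3 mm are ordinary. The share that enters an unadjusted final-score comparison is the gap times the regression slope, which equals r if the SDs at the two times are alike. For r from 0.3 to 0.6, a gap of 2 to 3 mm shifts the estimate by 0.3 × 2 = 0.6 mm to 0.6 × 3 = 1.8 mm.

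**6. If the SDs are for change instead.** With equal variances at both times, the variance under ANCOVA relative to a change-score analysis is (1 + r)/2, for example 0.75 at r = 0.5. There is then a gain at any r below 1, but the table in step 3 does not apply.

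**The case against.** **Silence is not an unadjusted plan.** A reader might infer that the article prescribes a plain comparison of means. It does not: an ANCOVA is also a comparison between the groups, and the t-test is named only for micro-perfusion. Sizing on raw means and then adjusting in the analysis is common and conservative. The multilevel sentence could even be read as a repeated-measures model of the outcome, although it is tied to rescue use and does not mention baseline VAS. A journal article may leave covariates to the full protocol or SAP. This objection stands against calling the text an error. It does not remove the case for naming the method: the article names methods for micro-perfusion and rescue medication, and none for the primary outcome.

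**The shortfall is small and its recovery uncertain.** A reader might infer that adjustment would more than make up for withdrawals. With SDs 12 and 13, unadjusted power is 89.5%, so there is almost nothing to recover. With SD 13, recovery needs r of about 0.29, and at r = 0.2 power is still only 88.4%. The 20 mm entry floor and rescue ibuprofen could both lower r. This stands, so the gain can only be stated conditionally.

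**Imbalance does not bias the trial.** A reader might also infer that a 2 to 3 mm baseline gap shifts the result by 2 to 3 mm. Only the slope's share enters. That variation is already in the standard error, and randomisation keeps the unadjusted test valid. This stands too. What remains is a loss of precision.

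**Conclusion.** The point holds as a free improvement. Baseline VAS is available on every patient, and nothing in the sizing or the stated primary analysis uses it.

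The size of the gain rests on r, on 67 completers per arm, on a true 7 mm difference and on the SDs being for final scores. Under those assumptions it is about 1 power point at r = 0.2 and about 3 at r = 0.3. At r = 0.5 it is 6.5 points with SDs 12 and 13, or 7.5 with SD 13. If r is near zero, adjustment costs one degree of freedom and almost nothing else.

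The documents do not support saying that the plan fixes an unadjusted analysis, that such an analysis would be invalid, or that adjustment is sure to offset the withdrawals.

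**What to change.** Before unblinding, state the primary analysis in one sentence. Either of these would do:

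- ANCOVA of follow-up VAS at a named primary visit, with treatment and baseline VAS as terms; or
- a repeated-measures model over the follow-up visits with baseline VAS as covariate, and the treatment contrast at a named visit.

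Report the adjusted mean difference with its 95% CI. In the Sample size section, say whether the SDs are for final scores or for change. If credit for adjustment is wanted, state the assumed r and its source.

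The cost is a few words, with no new data, visits or patients. Two corrections are still needed separately: the inflation for 20% withdrawal (92 per arm from 73, not 84) and the printed difference of 0.7, which does not agree with means of 30 and 23 mm.

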### Interventions

Eligible patients will be randomized into the following two groups: the Jingui external lotion group (treatment group) and the placebo lotion group (control group). The enrolled patients will be administered lotions via fumigating and washing externally for 2 weeks on both knees. DCE MRI examination will be performed at baseline and 2 weeks after the intervention is completed. The participants will be given personal instructions for using the lotions by our research nurses, who will be trained before the study. Patient visits will be performed at baseline and at 1, 2, and 4 weeks after treatment. Assessments including the VAS score for pain, Western Ontario and McMaster Universities Index (WOMAC) score and complications will be made during all four visits on the study knee.

The treatment group will receive Jingui external lotion, to be used twice a day (morning and evening, approximately every 12 hours and at the same time each day) for 14 consecutive days. The Jingui external lotion will be made according to the following procedure: a mixture of TCM (composed of *Semiliquidambar cathayensis* 60 g, *Radix zanthoxyli* 60 g, *Radix aconiti kusenzoffii* 30 g, *Radix aconite* 30 g, *Tinospora sinensis merr* 30 g, *Erythrina indica lam* 30 g, *Rheum officinale* 30 g, *Cassia twig* 30 g) will be boiled in 300 ml water, reduced to 150 ml of liquid medicine, and cooled to approximately 40°C. These hot liquid medicines will be administered as Jingui external lotion to the patients’ knees.

The control group will receive placebo lotion containing a food coloring agent and a small amount of Rheum officinale that is identical to the treatment group in terms of color and odor. The manufacturing and treating procedure are the same as the treatment group.

The research nurses will be involved in the treatment procedure to ensure the correct treatment is administered and that the temperature of the lotions is tolerable to the patients. During the process, when patients experience moderate pain or VAS score over 30 mm, ibuprofen sustained-release capsules will be administrated as rescue medication. Rescue medication consumption and time will be recorded in each randomized group when used. The patients will not be allowed to use other drugs aimed at treating KOA.

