### Outcome measures

#### Primary outcome measure

The primary efficacy endpoint of the study will be VAS, which is a pain score ranging from 0 mm (no pain) to 100 mm (worst pain ever experienced) [19], measured during all the assessment visits (baseline and 1-, 2-, and 4-week follow-up). The VAS score is usually a horizontal line, 100 mm in length, anchored by word descriptors at each end. Patients mark the point of their current pain on the line. The VAS score is then determined by measuring in millimeters from the left end of the line to the point that the patient marked.

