#### Secondary outcome measure

The secondary efficacy endpoint of the study will be rescue medication, WOMAC score [20] and micro-perfusion alteration in the patellar fat pad, femur and tibia subchondral bone.

Rescue medication complicates the interpretation of trial results by having an effect on the trial outcome. It is also possible to use rescue as a trial outcome. This is common in trials of treatments for asthma, where use of β_2_-agonists for rescue therapy may be a secondary trial outcome [21]. Rescue medication in this trial is Ibuprofen, which is a short-term nonsteroidal anti-inflammatory drug. We assume that the use of rescue medication varies with time in subjects in response to worsening of their disease. Consumption and time the subjects use rescue medication will be recorded in each randomized group.

The WOMAC score is a widely used proprietary set of standardized questionnaires used by health professionals to evaluate the condition of patients with osteoarthritis of the knee and hip, including pain, stiffness, and physical functioning of the joints. The index measures five items for pain (score range 0 to 20), two for stiffness (score range 0 to 8), and 17 for physical function (score range 0 to 68). It will be measured during all the assessment visits (baseline and 1-, 2-, and 4-week follow-up).

To assess micro-perfusion alteration, two parameters will be used: 1) maximum upslope represents the initial uptake of gadolinium into the region measured by finding the fastest uptake in the first few minutes after injection; 2) an enhanced rate represents the efflux rate constant from the extravascular extracellular space to plasma, which provides an index of venous hypertension and represents the ratio of the permeability surface area product over the extravascular extracellular space. With the mean curve function, maximum upslope and enhanced rate in the distal femur and tibia plateau subchondral regions of interest, and the infra-patellar fat pad and supra-patellar fat pad regions of interest will be measured and assessed.

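### The one model named for a clinical outcome adjusts for rescue ibuprofen, which pain itself triggers, so its treatment coefficient is neither the intention-to-treat effect nor an unbiased no-rescue effect

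*Protocol article*

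**What the plan says.** Four statements in the article bear on this.

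- **Trigger** (Interventions): "when patients experience moderate pain or VAS score over 30 mm, ibuprofen sustained-release capsules will be administrated as rescue medication". This is the scale of the primary outcome (Primary outcome measure): "The primary efficacy endpoint of the study will be VAS".
- **Nature of rescue** (Secondary outcome measure): "We assume that the use of rescue medication varies with time in subjects in response to worsening of their disease". The same section says "Rescue medication complicates the interpretation of trial results by having an effect on the trial outcome".
- **Rescue as an outcome** (Secondary outcome measure): "The secondary efficacy endpoint of the study will be rescue medication, WOMAC score", followed by micro-perfusion.
- **Analysis** (Statistical analysis): the section opens with "The data will be collected and analyzed according to the intention-to-treat principle". Later it says "Primary outcome will be compared between both groups", with no method. The next sentence promises a description of rescue use by arm. For comparing the outcomes that lie beneath rescue use, it adds: "so we adopt a multilevel regression approach with rescue as a time-dependent covariate". The only other named method is a t-test, for micro-perfusion.

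**The concern.** A covariate can safely enter a treatment comparison if treatment does not affect it, as with a baseline value. Rescue use does not qualify. By the article's own account it is started by pain, it changes pain, and it is an efficacy endpoint. If the lotion works, fewer lotion patients will need ibuprofen.

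With rescue in the model, patients are compared at equal rescue use. Two things follow.

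- The part of the benefit that shows as fewer patients crossing the pain threshold is partly removed, so the coefficient is not the intention-to-treat effect.
- Visits with rescue are visits with high underlying pain, so the rescue coefficient mixes the ibuprofen effect with the reason ibuprofen was taken. The treatment coefficient is then biased for the no-rescue effect as well. A random patient effect allows for dependence within patients but does not remove this visit-level confounding by indication.

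At stake is the size of the reported lotion effect, should this model's treatment coefficient be read as an efficacy result.

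**Working it through.** The article gives no figure for this analysis, so the size can only be illustrated.

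**Inputs from the Sample size section.** Means 30 and 23 mm, SDs 12 and 13, 73 per group, two-sided 0.05. The text attaches 23 mm to placebo; I assume that the lotion is the better arm, so control is 30 and lotion 23. The printed difference of 0.7 is read as 30 - 23 = 7 mm. With common SD = √((12² + 13²)/2) = 12.51, 73 per group gives power 0.919 (noncentral t), close to the stated 90%. A difference of 0.7 would need about 6,712 per group.

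**Does treatment affect rescue?** Chance of exceeding 30 mm at a given visit:

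- control: P(N(30, 12) > 30) = 0.50
- lotion: P(N(23, 13) > 30) = 1 - Φ(7/13) = 0.295

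The difference in rescue use with full uptake is therefore d ≈ 0.50 - 0.29 = 0.21.

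**Assumptions not in the article.** Random-intercept VAS at three visits, SD 12.51, no-rescue effect -7 mm, within-patient correlation 0.5, ibuprofen benefit b of 0, 5 or 10 mm, and rescue taken by everyone above 30 mm. In case (a) the trigger is the same pain state as the visit VAS. In case (b) it is a separate flare between visits.

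**Formulas.** With g the fitted rescue coefficient:

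- unadjusted effect U = -7 + b·d
- adjusted effect A = U + g·d
- g = c - b, where c is the excess underlying pain at rescue visits, hence A = -7 + c·d

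| Case | b (mm) | U | g | A | c = g + b |
|---|---|---|---|---|---|
| (a) | 0 | -7.08 | 18.65 | -3.12 | 18.65 |
| (a) | 5 | -6.11 | 13.59 | -3.08 | 18.59 |
| (a) | 10 | -4.84 | 8.51 | -3.03 | 18.51 |
| (b) | 0 | -7.12 | 5.51 | -5.94 | 5.51 |
| (b) | 5 | -6.21 | 0.37 | -6.13 | 5.37 |
| (b) | 10 | -4.76 | -4.70 | -5.73 | 5.30 |

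Check of the formula: (a) -7 + 18.6 × 0.21 = -3.1; (b) -7 + 5.4 × 0.21 = -5.9. Both agree with the simulation. The loss against -7 is c·d, which is positive whenever patients in more pain take rescue and the lotion reduces rescue.

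**Range.** Over 30 scenarios (correlation 0.3, 0.5, 0.7; b from 0 to 15 mm; full uptake), A ran from -2.67 to -3.86 in case (a), or 38-55% of 7 mm. In case (b) it ran from -5.45 to -6.50, or 78-93%.

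**Partial uptake, case (a), correlation 0.5, b = 0** (same simulation, run again):

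- 80% uptake: d = 0.173, g = 14.58, A = -7.06 + 14.58 × 0.173 = -4.54 (65%)
- 60% uptake: d = 0.128, g = 12.39, A = -7.11 + 12.39 × 0.128 = -5.52 (79%)

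**Direction against the effect regardless of rescue.** A is larger in size than U when g < 0, that is when b > c. In case (b) this happens above about 5.4 mm of ibuprofen benefit (for example -5.73 against -4.76). In case (a) it would need about 18.6 mm.

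**The case against.** **Scope.** The strongest objection is that the covariate model need not decide efficacy. The section commits to intention to treat, states the primary comparison in its own sentence, and brings in the multilevel model only in the sentence on rescue. That is right. A reader might infer that the primary VAS result will be rescue-adjusted, so that a working lotion would be reported at half its effect. The text does not say so, and an unnamed primary test is something that an article may leave to the full plan.

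**Already in the plan.** Rescue is already a secondary endpoint, with consumption and time recorded and its pattern reported by arm. This also stands, so part of the remedy is in place.

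**Specification unseen.** The article cites a source for the model that is not at hand. It does not say whether rescue is coded at the same visit, lagged or by interval, and the size of the bias depends on that. This limits the magnitude but does not remove the problem. The article describes an ordinary covariate and makes no provision for use triggered by the outcome.

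**Ibuprofen works.** If it does, the unadjusted difference understates the no-rescue effect, and the adjusted estimate can lie nearer to it (case (b), b = 10: -5.73 against -4.76, target -7). This stands. It shows that the two analyses answer different questions; it does not make the adjusted one valid for either.

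**Significance.** A reader might also infer that halving the estimate destroys power. The simulation does not support that, because the rescue term also reduces residual variance. In 60 simulated trials per setting at 73 per group, the adjusted model was significant in 88-98% and the unadjusted in 93-100%. The damage is to the estimate and its meaning.

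**Conclusion.** The concern holds within limits and should be fixed. Followed as written, the rescue-covariate model yields a treatment coefficient that is not the intention-to-treat effect and is biased for the effect without rescue. This follows from the article's own trigger, its own assumption about why rescue is used, and its listing of rescue as an endpoint.

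The size is illustrative. Relative to a 7 mm no-rescue effect, the model keeps about 40-55% with a same-state trigger and full uptake, about 65-79% with that trigger at 80% or 60% uptake, and about 75-95% with a separate flare. These figures rest on the planning means with the lotion as the better arm, and on an assumed correlation, uptake and ibuprofen benefit, none of which the article gives.

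A general claim of bias towards zero is not supported. Attenuation holds against the no-rescue effect; against the effect regardless of rescue, the error can go either way. Nor does the article make this the primary VAS analysis. The reason to act is that it is the only model named for a clinical outcome, while the primary comparison has no stated method, so nothing in the text keeps the two apart.

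**What to change.** Change the wording of the Statistical analysis section:

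1. State that the primary VAS comparison uses all observed VAS values regardless of rescue, with no rescue term in the model. This matches the intention-to-treat principle already declared.
2. Compare rescue between arms as its own outcome (for example any use, and amount taken), in addition to describing its pattern.
3. State that no efficacy conclusion will be drawn from the multilevel model with rescue as a covariate.
4. If an effect without rescue is wanted, make it a labelled sensitivity analysis, for example setting VAS after rescue to missing and multiply imputing under stated assumptions. An analysis of pain just before each rescue dose is not available from the described data: VAS is scheduled only at baseline and weeks 1, 2 and 4, and only consumption and time are recorded for rescue.

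The cost is analysis wording. VAS, rescue consumption and time of use are already collected, and neither the rescue rule nor any visit changes. There is a small downside: if ibuprofen relieves pain and control patients use more of it, the difference regardless of rescue will be smaller than the no-rescue effect (about 4.8 against 7 mm in the illustration with a 10 mm benefit and full uptake).
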